#### **4.2 Ethical consideration**

Before conducting this study, required permission to conduct this study will be obtained from the relevant institutions and participants. Ethical approval will be sought from the University of Cape Town Institutional Review Board. For carrying out the study in Rwanda, the approval will be sought from National Health Research Committee (NHRC), and Rwanda National Ethics Committee (RNEC). The study will also need permission from the hospitals. A signed informed written consent (Appendix xii) will be requested from each participant. For reviewing patients' records for baseline data of discharged patients, the written consent will be requested from the hospital superintendent, but after the intervention (training), the informed consent form will be requested from patients or parents/guardians for having access to the folders once he/she will be discharged and assent will be obtained from minors who have the capacity to give assent.

##### **4.2.1 Autonomy and respect**

Health care professionals and patient records will be treated as autonomous agents. Hospital superintendent information letter (Appendix vii) will be provided and their informed consent form (Appendix ix) will be requested from each hospital. Permission to access patient folders will be requested from patients or parents/guardians (Appendix xv). This will be done either on admission, or if not possible due to the condition of the participants, during their hospital stay.

Experimental hospital participant information letter (Appendix x) and comparator hospital participant information letter (Appendix xi) will be provided to all participants for them to read. A signed informed written consent (Appendix xii) will be requested from each health professional to show voluntariness and comprehension. Participation in the study will be voluntary, and health professionals will be free to withdraw from the study at any time without penalty or loss of benefits. Participants will be provided with information about the study so as to empower to make choice of participating in this study.

#### **4.2.2 Confidentiality**

Participants will be assured of confidentiality and anonymity. The codes will be used rather than the names on the health professionals' questionnaires and check list for medical records. Health care professionals, after filling the questionnaire, there will be a box provided in a safe area at every hospital to submit the questionnaires. Only the researcher had access to the collected raw data that will be kept in password protected computer files, and it will be kept in a safe area.

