### **3.1.4 Procedure**

The following steps will be taken in carrying out the feasibility study:

Ethical approval will be sought from the University of Cape Town Institutional Review Board. For carrying out the study in Rwanda, the approval will be sought from National Health Research Committee (NHRC), and Rwanda National Ethics Committee (RNEC). The study will also need permission from the hospital. Conveniently, the researcher will, one by one, meet the health care professional who fulfils the inclusion criteria for giving him/her a participant information letter, and those who will agree to participate will sign a written consent for agreement. This will avoid any unnecessary pressure to take part in the study. For reviewing patients' records for baseline data, the written consent will also be requested from the hospital superintendent, because patients will not be available during data collection, so permission of getting their records will be sought from the hospital superintendent. It will not be possible to obtain consent from individual patients to access

their records that have been discharged six months prior to the commencement of the study, provided that these participants will be no longer receiving care from the hospital. In their study, Zegers et al. (2007) reviewing patients records in Dutch hospital, the hospital superintendents have been consented to have access to patients records. After the intervention (training), the permission to access their folders will be requested from patients or parents/guardians. This will be done either on admission, or if not possible due to the condition of the participants, during their hospital stay. The training will be two full days and the researcher will be the one to carry out the training.

Prior to the training, the researcher will explain the title, aims, objectives, rationale and potential benefits and risks of the study. Written consent will be requested from health professionals before training. After agreement to participate in the feasibility study, the pre-test measurement will be performed.

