Power point presentations will be used during training. The majority of medical professionals in Rwanda have been trained and use English in their daily practice. For keeping the original content of the training, the presentation will be in English and, if it will be needed, the researcher will explain in local language (Kinyarwanda) or in French for more clarity. The training will be participatory; the trainees will be allowed to raise their opinions and questions at any time. Small group discussions and case presentations will be used during the training. After a case study, the practice will be done on the patients records' for demonstration. After training, the post-measurement of knowledge and attitudes on interprofessional practice will be performed in addition with training satisfaction questionnaire.

The training will be followed by a meeting between researcher and participants. The aim of the meeting will be to reach consensus on the training content, organisation, and training procedure and materials used in the training. In addition, the most appropriate methods to introduce the ICF conceptual framework into the routine management of patients within district hospitals will be identified. The meeting will also amend the outcomes measures.

The completed questionnaires will be deposited in the provided box that will be in the safe place within the hospital. After one week the researcher will collect the questionnaires from the box. The researcher will be also collecting discharge data from the medical records in orthopaedic/surgical, medical and paediatric wards. After collecting data, the researcher will organise the data for entry in the computer. After data entry and cleaning, the researcher will do data analysis.

Once the feasibility study has been conducted and the intervention has been finalised, the details of the intervention and amended informed consent documents will be submitted as an amendment for approval to the Faculty of Health Sciences Human Research Ethics Committee (HREC).

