### **3.1.5 Data analysis**

Data analysis will be performed using STATISTICA. Descriptive statistics will be used to describe the characteristics of health professionals, such as frequency and percentage, mean and standard deviation. Within-group analysis will be used. The dependent t-Test will be used to compare the means before and after intervention (training) to detect whether there are any statistically significant differences between two means. Data will be presented in forms of tables, Scatterplots, and graphs. The ICC for absolute agreement between the two raters' scores of the audit of patient records will be used to determine the reliability of the scoring. The accuracy of interpretation of folders will be indicated by a set of ten folders of patients discharged longer than 6 months ago, assessed by researcher and research assistant (s), Data entered and compared, discussion and consensus reached. A further 10 files assessed and this process will continue until 80% agreement is reached.

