- Monitoring knowledge (Appendix iii) and attitudes (Appendix ii).

- Auditing the quality of patient's records (Appendix v).

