#### **4.1 Data analysis**

Data will be entered into an Excel sheet by the researcher. For checking data entry error, ten percent of data will be double entered. The error of 5% will be set, above which the data would be double entered. Descriptive statistics will be used to describe the characteristics of the hospitals, health professionals and patients. Between-group analysis will be used to establish if the two sets of groups are equivalent at baseline and at two months, four months, and six months. Depending on the type of data and whether they are normally distributed, the chi-square, Mann-Whitney U or independent t-test will be used. Within group differences, to establish whether each group has altered over time will be done and will include McNemar's test, sign test and the dependent t-test. As cluster sampling has been done, multi-level regression analysis will be done to control for the effect of clustering. For comparison of the diagnosis categories of both groups will be performed using Chi-square test to ensure that there is no association between diagnosis and groups. If necessary, sub-group analysis will be performed post-hoc to explore the impact of diagnosis on the outcome measures. The data will be presented in forms of tables, Scatterplots, and graphs.

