**Case study:** Mr M.G is a 45 years old man, who is overweight and has type II diabetic patient. He is receiving insulin. He was admitted to the surgical ward four weeks ago, with an open mid-shaft fracture of the right femur caused by a road traffic accident. Mr M.G is cooperative under transtibial traction and wound dressing. His occupation is a driver and he is married, with four children. Mr M.G is very concerned about the condition because he is not sure if he will go back to his job in order to support his family and to involve in church activities. The hospital has a shortage of bed adjustable available to assist him in some bed activities, consequently, due to difficulty in bed mobility, he cannot wash, dress, feed himself, and has problem with toileting. His wife is taking care of their children, so he does not have a caregiver to help in all activities of daily living which is a requirement for in-patients in hospitals. Therefore, it is difficult to get the food. Members of the community visit him once a week to help in washing, changing dress, and bringing food. Mr M.G used to smoke 20 cigarettes a day and has developed pressure sores on his buttocks, limited right leg muscle strength and knee motion, and pain on fracture site. However, he is fortunate to have a medical insurance which helps in accessing all prescribed treatment.

Based on the above case study, please complete the following table. Indicate which problems described in fall under impairments, activity limitations or participation restrictions and environmental barriers or facilitators. You should also indicate the professional who should take responsibility for managing these problems, personal and environmental factors underlying M.G problems in the 2nd column. Finally you need to describe the probable management of this problem in the 3rd column.

| Health condition                                         | Profession | Management |
|----------------------------------------------------------|------------|------------|
|                                                          |            |            |
|                                                          |            |            |
|                                                          |            |            |
| Impairment                                               | Profession | Management |
|                                                          |            |            |

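### The free-text knowledge test (Appendix iii) has no marking key, named marker or masked marking, and as written only the researcher who delivers the training has access to the answers

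*Combined protocol and SAP*

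**What the plan says.** **The test.** Appendix iii presents one patient case and a blank table. The instruction is "Based on the above case study, please complete the following table". Staff write in the problems under each ICF component, the profession responsible and the management. The appendix gives no model answers, maximum score or marking rule.

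**Its use.** Section 1.4.2 makes change in knowledge an objective. Section 4 lists Appendix iii among the post-training measurements, and data are collected in both arms at two, four and six months. A baseline knowledge measurement is also planned, although the pre-training list cites other appendix numbers for it.

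**Return and handling.** Section 4.2.2: "Health care professionals, after filling the questionnaire, there will be a box provided in a safe area at every hospital to submit the questionnaires". The same section says "Only the researcher had access to the collected raw data". Section 4.1 adds "Data will be entered into an Excel sheet by the researcher". In the feasibility study, "After one week the researcher will collect the questionnaires from the box" (section 3.1.4). Section 4, however, has research assistants collecting the staff data.

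**Training.** For the feasibility study, "the researcher will be the one to carry out the training" (section 3.1.4). Section 4 bases the main-trial training on that procedure, with a further assistant helping the researcher. Comparator hospitals receive only a basic introduction to the ICF.

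**Safeguards.** Section 4 provides a blinded assistant to audit the records. Section 3.1.5 plans rater agreement for the same audit: "The ICC for absolute agreement between the two raters' scores of the audit of patient records". Neither safeguard is extended to Appendix iii.

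**The concern.** A free-text answer has no score until somebody gives it one. If that person taught the material and knows which hospitals were trained, doubtful answers may be credited more readily in one arm. If staff can look things up while answering, those who attended a two-day course have more to look up. Either effect would raise the experimental arm's knowledge score without any gain in what staff know or can apply unaided. The between-arm difference would then mix knowledge gained with access to material and with the marker's expectations, and the trial could not separate them.

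**Working it through.** The plan gives no score range, standard deviation or sample size for the knowledge score, so there is no figure to reproduce. The check compares the provisions for the two outcomes that need human judgement.

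| Feature | Record audit | Knowledge test (Appendix iii) |
|---|---|---|
| Response form | Mostly yes/no/not-applicable items, with two counts (Appendix v) | Free text in a blank table |
| Who scores | A trained assistant (section 4) | Not stated |
| Masking of the scorer | Yes (section 4) | Not stated |
| Agreement between scorers | ICC, and rounds of ten folders until 80% agreement (section 3.1.5) | None |
| Conditions of completion | Not applicable | Not stated; return by box |

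**Do other provisions fill the gap?**
- Cronbach's alpha above 0.70 (section 2.2.4.2) concerns consistency between items, not between markers.
- Double entry of ten percent of the data (section 4.1) checks transcription, not judgement.
- Codes replace names (section 4.2.2), but they are not said to hide hospital, arm or occasion.

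**Who could mark, under the plan as written?**
1. Section 4.2.2 confines access to the collected raw data to the researcher.
2. Section 4.1 has the researcher enter the data.
3. Sections 3.1.4 and 4 make the researcher the trainer, who therefore knows each hospital's arm.
4. So the only person with stated access to the answers is an arm-aware trainer. This follows from the access rule; no sentence assigns the marking.

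**Would the analysis remove such a bias?** Let d be the true difference and b a shift (in SD) that arises only in trained hospitals after training. With 4 hospitals per arm, m staff per hospital and intracluster correlation r:

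- expected difference = d + b
- SE = √{2[1 + (m − 1)r] / (4m)}, in SD units

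The shift b does not depend on m or r, so neither more respondents nor multi-level regression removes it. A baseline measurement does not remove it either, because it arises after training.

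**Illustration only.** Assume d = 0, b = 0.2, and a two-sided 5% t test on hospital means with 6 degrees of freedom.
- m = 20, r = 0.10: SE = √(2 × 2.90/80) = 0.269; chance of a significant result about 0.10.
- m = 94, r = 0.01: SE = √(2 × 1.93/376) = 0.101; chance about 0.38.

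The value 94 is the sum of the average staffing in section 3.2.2 (10 + 80 + 2 + 1 + 1), so it is an upper limit. The values of b, r and the lower m are assumptions. The illustration shows how a bias would act and is no evidence that b is 0.2.

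**The case against.** The best defence is that much of this is silence in a plan written before its tools are final. Section 3.1.4 says the outcome measures will be amended after the feasibility training, and section 3.2.2.2 defers the sample size until they are settled. A key might be added then. That is fair as to stage, but no section promises a key or masked marking, while the access rule is already written.

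Four stronger readings are tempting, and the documents do not support them.
- *The researcher alone handles the questionnaires.* Section 4 has research assistants collecting staff data. The exclusive wording in section 4.2.2 covers access to raw data and sits in a confidentiality clause. The two sections need reconciling.
- *Staff complete the test unsupervised over a week.* The box describes return, not completion. The one-week interval appears only in the feasibility procedure.
- *The trainer is assigned to mark, and will mark leniently.* No marker is named, and entering data is not scoring. Leniency is a risk, not something the plan shows.
- *Open-book answering helps only the trained arm.* Both arms could consult colleagues or notes, both see the ICF headings printed on the test, and comparators receive an introduction. What remains is a difference in degree: experimental staff receive the full course and discuss new record forms. Appendix vii uses nearly the test's headings, though both simply follow the ICF components.

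The drop box also serves anonymity, and section 3.1.4 seeks to avoid pressure on staff. Both count against imposing supervision without thought.

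**Conclusion.** The point holds as a gap in how the knowledge outcome is measured. Appendix iii requires judgement; the plan provides no key, marker, masking or rater check; and its access rule leaves an arm-aware trainer as the only person placed to judge the answers. Completion conditions are also open, with somewhat more scope for help in the experimental arm.

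The size and even the presence of bias cannot be determined from the documents. The conclusion rests on two inferences: that the researcher trains in the main trial as in the feasibility study, and that the raw-data rule applies to completed questionnaires.

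A reader might infer that the trial's main result is compromised. It is not on this ground: section 3.2.2.2 names interprofessional practice and comprehensiveness of records as the primary outcome, and the record audit has a masked assessor. The change should be made because knowledge is a stated objective and the remedy is cheap, but the trial does not stand or fall on it.

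**What to change.** 1. **Key.** Settle a marking key and score range for Appendix iii during the feasibility study.
2. **Masking.** Give each script a code that hides hospital, arm and occasion, and shuffle all occasions together before marking.
3. **Marker.** Have an existing research assistant not involved in training mark the scripts against the key. Amend section 4.2.2 to allow access to masked scripts, and reconcile it with section 4 on who collects the staff data.
4. **Agreement.** Double-mark a small random subset with existing assistants and report the ICC. Acknowledge that trained staff's vocabulary may still reveal the arm; codes cannot hide that.
5. **Completion, where feasible.** Have the assistants who already collect staff data give Appendix iii closed-book in one sitting, identically in both arms, and collect it under code. The blinded record auditor should not do this, since visits to trained hospitals could reveal the arm. Keep the box for the attitude and satisfaction forms.

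**Cost.** The cost is a short addition to section 4, a small change to section 4.2.2 and the assistants' marking time. The sitting is secondary to masked marking: it must be scheduled around shifts, may lose some respondents, and has to be weighed against the anonymity that the box gives.

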#### **4.2.3 Beneficence**

The potential beneficence and expected risk of the study will be well explained to the health professionals who will participate in this study. This study may help inform policy in enhancing an interprofessional practice and holistic care of patients and enhance collaboration between health care professionals. No physical, psychological, social, legal and economic risk which is expected during this study.

#### **4.2.4 Justice**

For achieving social justice, a cluster randomised control trial will be used and all experimental hospitals will be treated equally in terms intervention and data collection. If the intervention is found to be effective, similar training will be offered to those hospitals in the comparator group who wish to participate.

[figure not shown]

## 5 APPENDICES

### 5.1 Appendix i: Study outcome framework

| Quality of in-patient patient care                                                 | Training content | Practice/ Behaviour | System changes | Knowledge | Attitudes |
|------------------------------------------------------------------------------------|------------------|---------------------|----------------|-----------|-----------|
|                                                                                    | Training of HCP  | Patients Records    | Frame-work     | HCP       | HCP       |
| Comprehensive assessment                                                    |                  |                     |                |           |           |
| Health condition and diagnosis seen in ICF context                                 |                  |                     |                |           |           |
| Personal factors including mental and spiritual needs                              |                  |                     |                |           |           |
| Assessment of impairment                                                           |                  |                     |                |           |           |
| Assessment of functioning                                                          |                  |                     |                |           |           |
| Assessment of environmental factors                                                |                  |                     |                |           |           |
| Holistic intervention                                                       |                  |                     |                |           |           |
| Health condition managed in context                                                |                  |                     |                |           |           |
| Personal factors including mental and spiritual needs                              |                  |                     |                |           |           |
| Impairment addressed                                                               |                  |                     |                |           |           |
| Functioning addressed                                                              |                  |                     |                |           |           |
| Environmental factors addressed                                                    |                  |                     |                |           |           |
| Continuum of care                                                           |                  |                     |                |           |           |
| Prevention of recurrence of health condition or complications related to condition |                  |                     |                |           |           |
| Referral to community services                                                     |                  |                     |                |           |           |
| Liaison with community based services                                              |                  |                     |                |           |           |
| Interprofessional practice                                                  |                  |                     |                |           |           |
| Referrals to other discipline                                                      |                  |                     |                |           |           |
| Coordination of different services                                                 |                  |                     |                |           |           |
| Case discussion and interprofessional treatment planning                           |                  |                     |                |           |           |
| Integrated interprofessional ward rounds                                           |                  |                     |                |           |           |
| Task sharing and shifting                                                          |                  |                     |                |           |           |

